### Statistical analysis

Baseline comparability between the two treatment groups will be evaluated with respect to disease characteristics, demographics and baseline values of self-report measures. Chi-square or Student t-test, as appropriate, will be used for these comparisons, although decisions to adjust for one or more of the base line characteristics in the actual analyses will not be based on statistical significance but on the relevance of the confounding effects in case of imbalance occurring in spite of the balanced randomization procedure. The analysis will be performed in accordance with the "intent-to-treat principle", analyzing all patients within their randomization groups, regardless of whether they completed the allocated treatment. Intent-to-treat analysis often leads to smaller observed treatment differences, thereby increasing the risk of type I error (claiming there is non-inferiority/equivalence, when there is not). Therefore, a per-protocol analysis is also carried out and differences in results will be described.

The analysis will consist of assessment of differences in outcome measurements between both groups and differences in time to recovery. It will take into account the stratification factors (center; research nurse) as covariates in accordance with ICH E9. Other base line covariates, measured before randomization, may be incorporated into the analysis models to increase power and to remove any residual confounding. An assessment of interaction between the treatment on the one hand and the stratification variables, or. main baseline covariates, will be considered as a mandatory part of the primary analysis and a proper interpretation of efficacy. The "difference" between the two treatment arms, the treatment effect (on the appropriate scale) will be reported both as an overall (adjusted) value and – in the case of significant effect modification – in terms of its dependence on the categories or values of the effect modifiers. A significant interaction between the stratifying factors or main baseline covariates will be considered as part of a proper modeling strategy and will not imply correction for repeated significance testing. After fitting the proper model, inference on the treatment effect will be based on the smallest fitting model that allows estimation of the treatment effect.

When analyzing the primary outcome measure, Roland, the primary analysis will be a repeated measurement analysis of variance, hence estimating the original measurements. As a secondary analysis of this primary outcome variable, we will define "Roland-recovery" as a change of at least 11 points between baseline and any point in time post randomization. This dichotomization of the Roland score will be used as the outcome variable in a Cox regression analysis modeling time till recovery. The multivariate analysis will be performed along the same principles for variable selection and model building as outlined above.

A subgroup analysis is preplanned and will be performed to assess differences in treatment effect in subgroups of patients. (Table 4)

**Table 4 T4:** Prognostic variables in subgroup analysis

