**Discussion:**

Open discectomy is still considered to be the golden standard in the surgical treatment of lumbar disc herniation. Whether Percutaneous Laser Disc Decompression has at least as much efficacy as the standard surgical procedure, and is more cost-effective, will be determined by this trial.

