### Primary outcome measure

Roland Disability Questionnaire for Sciatica (RDQ) is an illness-specific 23-item functional assessment questionnaire that is frequently used for low back pain and sciatica [8-11]. The score, ranging from 0 to 23, reflect a sum of items experienced by the patient. The higher the score the more disabling the sciatica is perceived. The score will be analyzed as a continuous outcome variable. For descriptive purposes, "Recovery" (at the individual level) is defined by a difference of at least 11 points from baseline. A difference of 4 points for the averages between the two randomization arms is considered the maximum for "equivalence" of the two treatment modalities. The RDQ has established validity, reliability and responsiveness to change [12]. This outcome measure is used to determine the power of the study.

Other parameters that will be used from primary endpoint analyses are:

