#### 6) Incidence of re-operations

The incidence of re-operation will be used as an outcome measure.

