### Sample size

The study is designed as an equivalence study with asymmetric boundaries, leading to a non-inferiority design. A difference of 4 on the Roland Disability Questionnaire has been recognized as the minimum clinically important difference. The power calculation is performed under the alternative hypothesis of a difference of 1 point on the Roland scale. By using this value 4 as the upper limit of the equivalence interval, with α-level of 0.05, a power of 0.90 and a SD of 5, the required sample size was 98 (49 per treatment arm). To adjust for an 8% loss to follow up, we plan to include 110 patients. These calculations are based on a comparison of average at single points in time. By using a repeated measurements analysis of variance, the power of the study over the entire follow-up period will be substantially higher (or equivalently, the average difference between the treatments can be established more accurately).

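### A non-inferior intention-to-treat result would support PLDD with later surgery where it fails, not necessarily PLDD itself, and the per-protocol check carries no weight in the decision

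*Protocol article*

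**What the plan says.** The Statistical analysis section of the protocol article sets the comparison as intention to treat, "analyzing all patients within their randomization groups, regardless of whether they completed the allocated treatment". The primary analysis of the RDQ is a repeated-measures analysis of variance, and no exception is made for scores recorded after a re-intervention.

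The same section warns that intention to treat tends to shrink differences and so raises the chance of wrongly claiming non-inferiority. Its response is that "a per-protocol analysis is also carried out and differences in results will be described". It does not say what follows if the two analyses disagree.

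A secondary Cox analysis models time to recovery, defined as "a change of at least 11 points between baseline and any point in time post randomization". Re-intervention appears only as a separate secondary endpoint: "The incidence of re-operation will be used as an outcome measure".

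The target is worded in two ways. The abstract's Methods and the Outcome assessment section speak of comparing treatment strategies. The abstract's Discussion puts the question as "Whether Percutaneous Laser Disc Decompression has at least as much efficacy as the standard surgical procedure", and the opening of Methods/Design aims at non-inferiority of PLDD to surgical treatment. The description of arm B contains no surgery-on-failure step.

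**The concern.** A patient whose PLDD fails and who is then operated on contributes post-operation RDQ scores to the PLDD mean. If the second procedure is a discectomy, the comparator's effect is credited to PLDD. In a non-inferiority trial this pulls the arms together, which is the anti-conservative direction.

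The exposure is greatest at 1 year, which the article calls its most important landmark, because re-interventions have had time to act by then. The Background also expects recovery of the sciatica after PLDD to be possibly slower, and the trial is open.

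What is at stake is the meaning of the headline claim. The plan recognises the hazard, but the safeguard it names cannot change the conclusion.

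**Working it through.** **Inputs from the article.** The design is non-inferiority: "The study is designed as an equivalence study with asymmetric boundaries, leading to a non-inferiority design". The margin M is 4 RDQ points: "A difference of 4 points for the averages between the two randomization arms is considered the maximum for 'equivalence' of the two treatment modalities". The planning difference is 1 point: "The power calculation is performed under the alternative hypothesis of a difference of 1 point on the Roland scale". The SD is 5, alpha 0.05, power 0.90, and the sample size 49 per arm.

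**Reproducing the sample size.** By the normal approximation, n per arm = 2 × SD² × (z₀.₉₅ + z₀.₉₀)² / (M − 1)² = 2 × 25 × (1.645 + 1.282)² / 9 ≈ 47.6, so 48. A noncentral-t calculation gives 49 per arm (power 0.904), which matches the stated 98. One-sided 0.025 gives 59 per arm and does not match. The stated alpha therefore works as one-sided 0.05, and that is used below.

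**Decision threshold.** SE = 5 × √(2/49) = 1.01. Non-inferiority is declared when the observed difference is below 4 − 1.645 × 1.01 ≈ 2.34.

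**Effect of re-intervention.** Let D be the difference (PLDD minus surgery) without re-intervention, f the excess re-intervention proportion in the PLDD arm, and g the mean RDQ gain that it brings.

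- Intention-to-treat difference: d = D − f × g
- P(declare non-inferiority) = Φ((4 − d)/SE − 1.645)

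The article gives neither f nor g, so both are assumed: f from 10% to 40%, g from 4 points (the margin) to 11 points (the plan's own recovery threshold). The SD is held at 5, and all re-interventions are taken to have acted by the visit analysed.

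With D = 4, PLDD alone is exactly at the margin and the rate at f = 0 is 5%. Each cell shows the masked difference f × g, then the false non-inferiority rate.

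| f | g = 4 | g = 8 | g = 11 |
|---|---|---|---|
| 10% | 0.4; 11% | 0.8; 20% | 1.1; 29% |
| 20% | 0.8; 20% | 1.6; 48% | 2.2; 70% |
| 30% | 1.2; 32% | 2.4; 77% | 3.3; 95% |
| 40% | 1.6; 48% | 3.2; 94% | 4.4; 99.7% |

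One cell in full: f = 20% and g = 8 give d = 4 − 1.6 = 2.4, and Φ(1.6/1.01 − 1.645) = Φ(−0.06) ≈ 0.48.

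With D = 5 (PLDD alone inferior), the rate at g = 8 rises from 0.4% without re-intervention to 15% at f = 20% and 70% at f = 40%. At one-sided 0.025 with D = 4, the 20% × 8 cell is 35% against a nominal 2.5%.

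**Dilution over visits.** Table 3 schedules the RDQ at weeks 2, 4, 6, 8, 12, 26, 38 and 52 within the first year. If, as an illustration, re-interventions affect only weeks 26, 38 and 52, an equally weighted average shifts by 3/8 of f × g. The 1.6 points in the worked cell become 0.6. At 8 weeks there may be little shift at all.

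**The case against.** The strongest reply is that the trial compares strategies and aims at cost-effectiveness. The costs of a second operation belong to the arm that generated it, so its benefits do too. That stands. A reader might infer that intention to treat is the wrong analysis here; the documents do not support that, since it is a legitimate target and matches much of their wording. The reply does not cover the claim about PLDD itself in the abstract's Discussion and Methods/Design.

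Second, the risk is named, and re-operation incidence would be reported beside the RDQ. This also stands, but a visible mechanism is not a decision rule.

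Third, the definition of the per-protocol set may sit in a fuller document. Agreed, and its absence is not a finding. A reader might infer that the set would drop PLDD failures and so be biased towards PLDD. The article does not define the set: patients who completed PLDD and were operated on later could equally stay in.

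Fourth, a reader might infer that the Cox model rewards failure. It models time to recovery, so a patient who recovers only after re-operation does so late, which lowers the PLDD hazard. The failure is partly penalised, though it can still count as a PLDD recovery.

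Fifth, requiring a re-intervention-as-failure analysis to pass as well would be costly. Take a true intention-to-treat difference of 1 point with a masked 30% × 8 = 2.4. That contrast is then about 3.4 against a threshold of 2.34, and power falls from about 90% to about 15%, with inclusion already complete. Carrying forward the last score before re-intervention would also fix a patient near the worst point and ignore uncertainty. Both arguments stand and shape the fix.

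**Conclusion.** The point holds in limited form. Scores after re-intervention count in the randomised arm; the article does not say so in words, but it follows from the intention-to-treat rule without an exception. A non-inferior result therefore supports PLDD followed by surgery where it fails, and not necessarily PLDD itself. The per-protocol analysis is given no role in the decision.

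The size cannot be derived from the documents. The range of about 11% to over 99% rests on assumed re-intervention rates and gains, on PLDD alone lying exactly at the margin, on SE 1.01, and on the 1-year visit. It is smaller at 8 weeks or averaged over visits. Only the excess over the surgery arm matters, so re-operations there offset part of it.

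A reader might take the upper end to mean that a non-inferiority finding would be produced by second operations. The documents support only that it could be. Severity: should be fixed; it does not invalidate the design.

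**What to change.** 1. Keep intention to treat as the comparison of strategies and as the basis for cost-effectiveness.
2. State that non-inferiority is concluded only if the upper confidence bound is below 4 in both the intention-to-treat and per-protocol analyses.
3. Prespecify a supplementary analysis that treats re-intervention in either arm as treatment failure. In the Cox model, a patient re-operated before recovery counts as not recovered. For the RDQ, apply a stated failure rule with a sensitivity range, not a single carry-forward.
4. If the supplementary analysis does not support non-inferiority, limit the conclusion to the PLDD-first strategy and report it beside the re-operation incidence. It should not be a third condition on the strategy claim.

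The cost is a few sentences and some extra model runs on data already being collected. The article reports follow-up continuing until at least the end of 2009, so the rule could have been set before the final analysis. The downside is a somewhat harder claim, because the per-protocol analysis must also pass, and possibly a narrower one.

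### The model behind the non-inferiority estimate is chosen after fitting, by a rule with no stated criterion, so the number compared with the 4-point margin is not fixed in advance

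*Protocol article*

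**What the plan says.** All the rules stand in the Statistical analysis section of the protocol article.

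- On the randomisation strata: "It will take into account the stratification factors (center; research nurse) as covariates in accordance with ICH E9".
- Other baseline covariates "may be incorporated into the analysis models to increase power and to remove any residual confounding". No list is given. Adjustment for a baseline characteristic is to depend on how relevant its confounding is judged to be when an imbalance appears, and not on a significance test.
- Assessing interaction of treatment with the strata or the main baseline covariates (also unlisted) "will be considered as a mandatory part of the primary analysis and a proper interpretation of efficacy". A significant interaction "will be considered as part of a proper modeling strategy and will not imply correction for repeated significance testing".
- An overall adjusted treatment effect is reported in every case. Effects by level of a modifier are added when the interaction is significant.
- Finally, "inference on the treatment effect will be based on the smallest fitting model that allows estimation of the treatment effect".

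The same section names a repeated-measures analysis of variance as the primary RDQ analysis, and carries the same selection and model-building rules over to the Cox analysis of time to recovery. Baseline RDQ is collected (Table 3) but is not named as a covariate.

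**The concern.** The trial's main conclusion turns on one number: the upper confidence limit for the RDQ difference, set against 4 points. Here the model that produces it is known only after fitting, and nothing states what makes a model fit or when it is small enough. Two analysts could follow the text faithfully and reach different limits. The design is open and the RDQ is patient-reported, so a conclusion near the margin would be hard to defend against the charge that the model was chosen to suit it.

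The text also pulls against itself. Centre and nurse are to be accounted for, yet a smallest-model rule could remove them. Significance is ruled out as the ground for baseline adjustment, yet it decides whether level-specific treatment effects are presented as part of the primary analysis.

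**Working it through.** **1. The plan's own figure.** Inputs from Sample size: "By using this value 4 as the upper limit of the equivalence interval"; "The power calculation is performed under the alternative hypothesis of a difference of 1 point on the Roland scale"; and "with α-level of 0.05, a power of 0.90 and a SD of 5". The article does not say whether alpha is one- or two-sided.

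- Normal approximation, one-sided 0.05: n per arm = 2 × 5² × (1.645 + 1.282)² / (4 − 1)² = 47.6, so 48 (96 in total).
- The noncentral-t version gives 49 per arm (98 in total), power 0.904. This matches the stated 98.
- One-sided 0.025 gives 59 per arm (60 by t) and does not match, so one-sided 0.05 is used below.
- The standard error of the difference at 49 per arm is 5 × √(2/49) = 1.01.

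**2. What selecting the model does to the error rate.** The simulation used 6,000 trials per setting, 49 per arm, SD 5, a true difference of exactly 4, one-sided 0.05, and one time point. It had ten balanced binary covariates unrelated to outcome, and a baseline RDQ correlated 0.3 or 0.5 with outcome. The correlations are assumed, as the article gives none. Strata and repeated visits were not modelled.

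| Model used | False non-inferiority, r = 0.3 | r = 0.5 |
|---|---|---|
| Unadjusted, fixed | 5.0% | 5.5% |
| Baseline RDQ only, fixed | 4.6% | 5.2% |
| Covariates kept if significant | 4.9% | 5.6% |
| Most favourable of 4 models | 7.1% | 8.5% |
| Most favourable of 24 models | 8.6% | 10.1% |

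The Monte Carlo standard error at 5% is √(0.05 × 0.95/6000) = 0.3 percentage points, so the first three rows do not differ materially from 5%. Only the last two rows, where the choice follows the result, show inflation.

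Across the 24 models the estimate ranged by a median of 0.6 points (r = 0.3) or 0.7 points (r = 0.5), with a 95th percentile of 1.2 or 1.4. The assumed difference and the margin are 4 − 1 = 3 points apart.

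**3. Uncorrected interaction tests.** With independent tests at 5%, the chance of at least one false positive is 1 − 0.95^k.

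- k = 2 (centre and nurse, the named factors): 9.75%, about 10%.
- k = 10 (if the main baseline covariates were the ten in Table 4): 40%.
- k = 12 (both sets): 46%.

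Such tests are also weak. For a balanced binary modifier the interaction standard error is 2 × 5 × √(2/49) = 2.02, so 80% power needs 2.80 × 2.02 = 5.7 points, more than the margin. With 110 patients in 8 hospitals there are about 6.9 per arm per hospital, and a hospital-specific 90% interval is ±1.645 × 5 × √(2/6.9) = ±4.4 points.

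**4. Baseline RDQ as a fixed covariate.** Residual variance is multiplied by 1 − r².

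- r = 0.3: variance falls 9%, standard error 0.96, 44 per arm needed.
- r = 0.5: variance falls 25%, standard error 0.87, 36 per arm needed.

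At 49 per arm, power rises from 0.904 to 0.926 (r = 0.3) or 0.961 (r = 0.5).

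**The case against.** The best defence is that the section limits the discretion itself. It keeps significance tests out of baseline adjustment, says that centre and nurse are accounted for, and always reports an overall adjusted effect. A detailed covariate list is commonly left to an analysis plan. All of this is true and lowers the stakes. It does not settle the point, because what the overall effect is adjusted for remains open, and the article states the smallest-model rule as the basis of inference rather than deferring the choice. That the rule would in fact remove centre or nurse is a possibility, not something the text says.

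Three stronger readings are tempting and are not supported.

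- **That selection by itself makes the confidence limits too narrow.** Selection blind to the treatment result left the error at 4.9–5.6%. The 7–10% figures require an analyst to pick the most favourable model, which the protocol does not plan.
- **That 40% of trials would show a false interaction, and about 20% a falsely non-inferior subgroup.** The simulation does give 20–21% for the latter, with ten modifiers and a true difference at the margin. But Table 4 belongs to a separately introduced subgroup analysis, and the article nowhere equates its variables with the main baseline covariates. Nor does it plan a non-inferiority decision within a subgroup: the Primary outcome measure section sets the 4 points for the averages of the two randomised arms.
- **That baseline RDQ has been made optional.** It is simply not named. A repeated-measures analysis might carry it as a time point.

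**Conclusion.** The point holds as a failure to fix the primary estimate, not as a demonstrated error inflation. The article bases inference on a rule without a criterion, leaves covariate entry to judgement after imbalance is seen, and places uncorrected interaction tests inside the primary analysis.

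Type I error stays near 5% if selection ignores the treatment result, and reaches about 7–10% if the choice among 4 to 24 models follows it. The chance of a false interaction is about 10% for the two named factors. The 40% figure depends on reading Table 4 into the primary analysis, and all these figures assume independent tests. The precision gain from baseline RDQ, a 9–25% cut in variance, rests on an assumed correlation of 0.3–0.5 and is a missed improvement rather than a mistake. The stated design already reaches 0.90 power without it.

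**What to change.** Replace the smallest-model sentence with one prespecified primary model for RDQ: treatment, visit, treatment-by-visit, hospital/nurse randomisation stratum, and baseline RDQ. State that no term is added or dropped after the data are seen. Draw the non-inferiority conclusion only from this model's overall treatment effect, meaning the effect in all randomised patients rather than in a subgroup.

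Move the interaction assessment out of the primary analysis and delete the sentence that waives correction. Report every interaction and subgroup result, significant or not, with confidence intervals, labelled exploratory and with no non-inferiority claim. Date the change before outcome data are analysed by arm.

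The cost is wording plus degrees of freedom: 8 − 1 = 7 for hospital, and more if nurse strata are separate, since the number of hospital/nurse lists is not given. On a single-visit basis with 98 patients, hospital and baseline RDQ take the residual degrees of freedom from 98 − 2 = 96 to 96 − 7 − 1 = 88. The sample size need not rise.

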### Outcome assessment

The assessment of outcome will use several validated outcome parameters as described below. Patients will undergo neurological examination by the research nurse at 4, 8, 26, and 52 weeks (Table 2). Questionnaires will also be filled out at these follow-up moments. At 1, 2, 6, 12, 38, 78, and 104 weeks the questionnaires will be filled out by the patient at home, and subsequently send to the data collection center by regular mail. Outpatient control by the neurosurgeon takes place at 8 weeks and thereafter if deemed necessary. The follow-up moments of data collection and outcome measures are listed in Table 3.

**Table 2 T2:** Neurological examination

*Straight leg raising test (Lasègue)
*Crossed straight leg raising test (Crossed Lasègue)
*Sensory loss
*Dermatome anesthesia
*Muscle weakness
*Knee tendon reflex difference
*Ankle tendon reflex difference
*Finger-ground distance in centimeter

Lasègue's sign is defined positive if the patient experiences a typically dermatomal area of pain reproduction and pelvic muscle resistance below a unilateral 60 degrees angle provocative straight leg raising. 'Crossed positive' if the same experience was noted with straight raising of the contralateral leg below 90 degrees.

**Table 3 T3:** Data collection and outcome measures

	RN			RN		RN		RN		RN		
**Time in weeks**	***X***	0	2	***4***	6	***8***	12	***26***	38	***52***	78	104

Treatment preference patient	v	v								v		v

Neurological examination	v			v		v		v		v		

Likert	v	v	v	v	v	v	v	v	v	v	v	v

Prolo	v			v		v		v		v		

Severity of complaints (VAS)	v	v	v	v	v	v	v	v	v	v	v	v

Functional status (Roland DQS)	v	v	v	v	v	v	v	v	v	v		v

McGill	v									v		v

Health status (Rand/SF 36)	v			v		v		v		v	v	v

EuroQol	v	v	v	v	v	v	v	v	v	v	v	v

SFB Index	v			v		v		V		v		

Costs (diary)	v		v	v		v	v	V	v	v		

Surgery/PLDD		v										

Complications		v		v		v		v		v		

"RN" marks the scheduled meetings with the Research Nurse.

Our goal is to show clinical equivalence between the two treatment strategies at various time points. The 1-year follow-up will be the most important clinical landmark. The cost-effectiveness analysis will therefore be performed using the clinical and economical parameters at 1 year.

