**MRI variables**
*Median versus mediolateral and lateral herniation
*High disc space versus low disc space
*Higher signal versus lower signal of disc on T2 weighted images
*Bud-herniation versus broad based herniation

Data will be stored via the internet-based secure data management system (ProMISe) of the department of Medical Statistics and Bioinformatics. The analysis will be carried out using SPSS.

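### If the primary repeated-measures ANOVA is run in its classical form, one missed questionnaire removes the patient; the plan should name a mixed model that uses every observed RDQ visit

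*Protocol article*

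**What the plan says.** The Statistical analysis section of the protocol article fixes the method for the primary outcome: "the primary analysis will be a repeated measurement analysis of variance, hence estimating the original measurements". The software is given at the end of that section, below Table 4: "The analysis will be carried out using SPSS". No SPSS procedure is named.

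The analysis population follows the intention-to-treat principle, "analyzing all patients within their randomization groups, regardless of whether they completed the allocated treatment".

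The Sample size section works from a comparison of means at one time point. It then allows for attrition: "To adjust for an 8% loss to follow up, we plan to include 110 patients". It adds that the repeated-measures analysis will give more power over the whole follow-up.

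Table 3 schedules RDQ before treatment (columns X and 0) and at weeks 2, 4, 6, 8, 12, 26, 38, 52 and 104. Weeks 4, 8, 26 and 52 are research-nurse visits. At the other times, according to the Outcome assessment section, questionnaires "will be filled out by the patient at home, and subsequently send to the data collection center by regular mail". The Abstract and Background make 8 weeks and 1 year the primary times, and Outcome assessment singles out 1 year as the main clinical time point.

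**The concern.** The usual meaning of the named method in SPSS is the repeated-measures option of the general linear model. It needs one complete row per patient and deletes any patient with a gap. Under that version, a form lost in the post at week 6 would also remove the same patient's 52-week score, although a nurse had collected it in person.

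Three things would be at stake:

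- **Precision at the primary times.** The attrition allowance suits an analysis in which each patient with a score at the time in question counts. It does not suit one in which a patient needs all nine scores.
- **Bias.** A complete-case comparison is safe only if having a full set of forms is unrelated to outcome, given group and covariates. Patients who do badly, or who recover and stop replying, may break that condition, possibly to different degrees in the two arms of an open trial. The article itself worries about a false claim of non-inferiority, but its per-protocol analysis addresses treatment received, not missing forms.
- **Standard errors.** The univariate within-patient tests of the classical method assume sphericity. That is hard to believe when gaps between visits run from 2 weeks to a year.

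**Working it through.** **Inputs from the article.** Margin 4 ("By using this value 4 as the upper limit of the equivalence interval"); true difference 1 ("The power calculation is performed under the alternative hypothesis of a difference of 1 point on the Roland scale"); SD 5; α 0.05; power 0.90; 49 per arm (98 in all); 8% loss; 110 planned. RDQ times after week 0: nine (eight up to week 52). Mailed: weeks 2, 6, 12, 38 and 104, so five of nine.

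**Input assumed.** Missingness per visit, p. The article gives none; 2% to 5% is used as an illustrative range, first with independence between visits.

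**1. The plan's own figure.** The distance from the assumed difference to the margin is 4 − 1 = 3. With one-sided α = 0.05, n per arm = 2 × [5 × (1.645 + 1.282)/3]² = 47.6, so 48. The noncentral t gives power 0.899 at 48 and 0.904 at 49, so 49 per arm reproduces. One-sided 0.025 would need 59 per arm and does not fit. For attrition, 98/0.92 = 106.5, so 107. The planned 110 tolerates 1 − 98/110 = 10.9% loss.

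**2. Complete cases if every post-treatment RDQ is required.** The complete fraction is (1 − p)^9. Single-time power is Φ(3/(5√(2/n)) − 1.645), with n half the patients left.

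| p per visit | Complete | Lost | Left of 110 | Single-time power |
|---|---|---|---|---|
| 1% | 0.914 | 8.6% | 100.5 | 0.91 |
| 2% | 0.834 | 16.6% | 91.7 | 0.89 |
| 3% | 0.760 | 24.0% | 83.6 | 0.86 |
| 5% | 0.630 | 37.0% | 69.3 | 0.80 |

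Break-even: 1 − 0.92^(1/9) = 0.9% per visit uses up the 8%, and 1 − (98/110)^(1/9) = 1.3% uses up the full 10.9%.

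**3. First year only.** With eight visits and p = 5%, 0.95^8 = 0.663 leaves 73 of 110, about 37 per arm. Noncentral-t power at a single time is then about 0.82.

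**4. Permanent loss plus scattered gaps.** 110 × 0.92 × 0.98^9 = 84 and 110 × 0.92 × 0.95^9 = 64. Single-time power is 0.87 and 0.77. If every patient with a score at that time were used, 110 × 0.92 = 101 would remain (about 50 per arm), with power 0.91.

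**5. Effect of clustering.** If all missed forms fell in the same patients, the loss would be p itself, 2% to 5%, which is inside the 8% allowance. The independent figures therefore lie towards the high end.

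**6. The contrast averaged over nine visits.** With a common correlation ρ (assumed), the SD of a patient's mean is 5√((1 + 8ρ)/9): 3.73 at ρ = 0.5 and 4.28 at ρ = 0.7. With the 84 and 64 patients of step 4, power is 0.98 and 0.94 at ρ = 0.5, and 0.94 and 0.88 at ρ = 0.7.

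**The case against.** The strongest reply is that the article never says a patient with a gap is excluded. The method name is generic and SPSS can also fit repeated measures with MIXED, which uses all observed visits. The talk of covariates, interactions and a smallest fitting model suits that version equally well. Handling of missing data is commonly left to a full protocol or analysis plan, neither of which is shown. This stands in part. Listwise deletion is an inference from the usual form of the named method, so the point must be conditional. It is not only a matter of missing detail, however: the article does name the primary method, and its ordinary form suits this visit schedule badly.

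A reader might infer that the plan contradicts its own intention-to-treat statement. It does not. That sentence concerns analysis as randomized whether or not treatment was completed, and says nothing about missing questionnaires.

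A reader might also infer that the primary analysis is underpowered. The figures do not support that. The 0.77 to 0.89 values at 2% to 5% missing are for a single-time comparison; step 6 shows that the averaged contrast may keep adequate power.

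Two further points stand. The missingness rates have no source in the article, and missed forms usually cluster. Both primary times are nurse visits, so equal missingness at every visit is a simplification. Finally, the between-arm test of each patient's mean does not need sphericity, so that concern is confined to the univariate within-patient tests.

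**Conclusion.** The point holds conditionally. If the named analysis is run as a classical repeated-measures ANOVA, 2% to 5% missing per visit would exclude about 17% to 37% of patients (92 to 69 of 110 left), against 8% allowed for. This rests on assumed rates and independence between visits; with complete clustering the loss would be only 2% to 5%.

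The consequences are some loss of single-time power at 8 and 52 weeks (about 0.82 at 37 per arm, against the planned 0.90) and possible selection bias in the non-inferiority comparison. The bias is the more serious of the two, because averaging over visits does not remove it. Its size and direction cannot be derived from the article.

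The wording should be changed because it permits an avoidable loss of observed primary-outcome data. The article does not show that this loss was intended.

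**What to change.** In the Statistical analysis section, replace the repeated-measures ANOVA with a likelihood-based linear mixed model for repeated measures (SPSS MIXED) that uses all observed RDQ visits. Include treatment, visit, treatment-by-visit, baseline RDQ, the stratification factors (center and research nurse) and a flexible covariance between visits. Report the 8-week and 52-week contrasts from this model, with their confidence limits set against the 4-point margin.

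Scattered gaps then remove nobody, and the 8% allowance keeps its intended meaning. The model still assumes that missingness depends only on what was observed, so a missing-data sensitivity analysis would be a useful but optional addition.

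The cost is slightly more analysis work in the same software. No new data are needed, which matters because the Discussion reports that inclusion is already complete.
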